##### Patient healthcare resource use and costs data (H_6_)

Inpatient healthcare resource use and costs will be recorded from the administration systems at participating hospitals for usual clinical care activities. In addition, resource use associated with HIRAID® Inpatient implementation will be recorded prospectively. Healthcare resource use will be costed from the perspective of the health service using actual costs or market rates. These data will be used to inform cost-effectiveness analyses.

##### Implementation fidelity (H_7_)

To address H7 (HIRAID® Inpatient is implemented with high fidelity (80%)), CNCs/CNEs employed to assist with education and rollout will be invited to evaluate implementation fidelity. All records of communication kept will be de-identified by the facilitator making the record. A copy of the participant information statement will be provided to all those involved in leading implementation. The HIRAID® implementation evaluation will be guided by the RE-AIM framework [46] and scoring instrument [47]. *Reach* will be measured by the proportion of eligible nurses participating in the programme, *effectiveness* through the end user (nurses’) opinions on the usefulness of HIRAID®, and *adoption* by the proportion of eligible sites implementing HIRAID®. *Dose* is the consistency of exposure to HIRAID® across settings and *fidelity,* the degree to which individual components and the overarching implementation strategy were delivered. *Sustainability* will be determined through demonstration of ongoing HIRAID® training programme use post implementation, along with the proportion of nurses reporting they use HIRAID® at ≥ 6 months.

#### Sample size

Sample sizes were calculated for each of the hypotheses. Hypotheses H1, H2, H3, and H6 sample size estimations were conducted collectively, as they will use medical record and cost data from relevant systems for the period of 1 st July 2026 to 1 st December 2027 (Table 4—shaded grey). To maximise the study’s power in detecting true differences, should they exist, the largest sample size estimation is reported and will be used. Sample sizes were calculated with an assumed intra-class correlation of 3%, 5% significance (two-tailed) and 80% power, and applying Woertman’s SW design estimate approach [48]. These sample sizes have been calculated using the most recent data from the study sites and/or previous work by the investigators in this field. To evaluate implementation fidelity HIRAID® facilitators (CNCs/CNEs) employed to assist with education and roll out will be invited to participate in the evaluation of implementation fidelity. The number of staff to be involved in this process will be determined by each LHD.

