### Phase 3: Implementation evaluation of HIRAID® Inpatient

#### Study design

In Phase 3, the HIRAID® Inpatient framework will be implemented using a Type II effectiveness-implementation hybrid design [29], including a SW-cRCT [30]. The hybrid approach allows testing of the implementation strategy at the same time as observing the outcomes of the intervention [29, 30]. Four clusters will be progressed through three sequential phases: control, intervention transition and post-intervention, with a staggered rollout and a 1:1 allocation ratio, with most data collected from each defined population as outlined in Table 4. The trial is structured within a superiority framework, aiming to demonstrate improved outcomes compared to usual care.

Each participating hospital ward (cluster) will begin in the control phase, representing a period of routine or usual care before the scheduled implementation of the HIRAID® Inpatient framework. During this phase, baseline data and behavioural diagnostics will be collected to serve as the comparator for the intervention. Rather than using a separate, concurrent control group, this SW-cRCT uses each cluster as its own control. Data gathered during the pre-intervention phase will be directly compared with data collected post-implementation. This design enables evaluation of the intervention against established, real-world clinical practice. The HIRAID® Inpatient intervention will then be implemented over a three-month period (Intervention Transition), followed by an intervention data collection period, lasting between 3 and 12 months, depending on the cluster (Fig. 3).

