**Fig. 3 Fig3:**
[figure not shown]
The stepped-wedge cluster randomised controlled trial design for the implementation of HIRAID® Inpatient across four clusters. Each sequence comprises a 3- to 12-month baseline control condition, a 3-month intervention transition period, and a 3- to 12-month intervention exposure condition

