#### Randomisation

Each cluster will be randomly allocated to one of four starting dates for implementation. Randomisation will be performed by the study statistician using computer-generated numbers. Participating wards will have no influence over the allocation prior to randomisation, ensuring concealment of the allocation sequence until wards are assigned. No further changes to clusters will be made once the allocation has been finalised to minimise the risk of bias.

We are unable to randomise sites to clusters because of geographical location and clinical governance. The significant geographical distance between sites, mitigates the risk of contamination due to reduced proximity. Randomising clusters based on health service provides consistent clinical governance for study operations.

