### Trial status

All ethical and governance approvals are in place at participating hospitals. The protocol is Version 5.0 dated 30th April 2025. Recruitment is scheduled to begin on the first of July 2026 and will be completed approximately on 31 st December 2027. The trial is prospectively registered with the Australia New Zealand Clinical Trial Registry ACTRN12625000639426 (registration date: 17/06/2025).

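### The record and cost window for H1, H2, H3 and H6 closes a month before the 18-month schedule; separately, the 6-month use measure does not fit the last cluster's 3 post-transition months

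*Protocol article*

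**What the plan says.** All references are to the protocol article.

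- **Sample size.** H1, H2, H3 and H6 are sized together because they share one data source, hospital records and costs for "1 st July 2026 to 1 st December 2027".
- **Trial status.** "Recruitment is scheduled to begin on the first of July 2026" and "will be completed approximately on 31 st December 2027".
- **Fig. 3 caption.** Each sequence has "a 3- to 12-month baseline control condition, a 3-month intervention transition period, and a 3- to 12-month intervention exposure condition".
- **Phase 3, Study design.** After a three-month transition, post-intervention data are collected for a period "lasting between 3 and 12 months, depending on the cluster".
- **Randomisation.** "Each cluster will be randomly allocated to one of four starting dates for implementation".
- **Implementation fidelity (H7).** Sustainability has two components. One is continued use of the training programme after implementation. The other is nurse-reported use: "along with the proportion of nurses reporting they use HIRAID® at ≥ 6 months". The section does not say from which date the 6 months are counted.

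**The concern.** A stepped-wedge schedule fixes how much exposed time each cluster contributes. If the data window is shorter than the schedule, the missing time comes off the end, when every cluster has already crossed over. The loss is then entirely post-intervention and takes the largest share from the cluster that crosses last. Four of the seven hypotheses that Table 1 lists as primary use this window. A data custodian asked for an extract would work to the printed dates.

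The sustainability measure raises a different question, because it comes from nurses' reports and not from the record extract. A time point of 6 months or more is set against a schedule that gives the last cluster only 3 months after transition. If this is left open, it is unclear which clusters the 6-month figure describes.

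**Working it through.** **Inputs.** Start 1 July 2026 and end about 31 December 2027 (Trial status). Record window to 1 December 2027 (Sample size). Control 3 to 12 months, transition 3 months, exposure 3 to 12 months (Fig. 3 caption). Four clusters and four start dates (Randomisation). ICC 0.03 (Sample size). 4,050 admissions per month across the study wards (Study setting). Fig. 3 itself is not shown, so the even 3-month steps used for the two middle clusters are inferred.

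**Step 1: reproduce the trial length.** With all clusters observed over the same calendar, the shortest control goes with the longest exposure:

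- first cluster: 3 + 3 + 12 = 18 months
- last cluster: 12 + 3 + 3 = 18 months

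Eighteen months from 1 July 2026 ends on 31 December 2027, which agrees with Trial status.

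**Step 2: length of the record window.** 1 July 2026 to 1 December 2027 is 17 months, 30 days short of 31 December.

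**Step 3: exposed time per cluster.** Months after transition = window length − control − 3.

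| Cluster (order) | Control | Exposure starts | To 31 Dec 2027 | To 1 Dec 2027 |
|---|---|---|---|---|
| 1 | 3 | 1 Jan 2027 | 12 | 11 |
| 2 (inferred) | 6 | 1 Apr 2027 | 9 | 8 |
| 3 (inferred) | 9 | 1 Jul 2027 | 6 | 5 |
| 4 | 12 | 1 Oct 2027 | 3 | 2 |
| Total | 30 | | 30 | 26 |

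Post-intervention time falls by 4/30 = 13%, while control time stays at 30. The last cluster goes from 3 months to 2, below the stated minimum. The loss of four cluster-months and the last cluster's figure do not depend on even steps. The total of 30 does.

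**Step 4: effect on precision.** A Hussey–Hughes model was used: cross-sectional, monthly periods with fixed period effects, ICC 0.03, total variance 1, transition months left out. The variance of the treatment effect was:

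| Patients per cluster-month | 18 months | 17 months | Ratio |
|---|---|---|---|
| 100 | 0.003726 | 0.003882 | 1.042 |
| 1,012 (about 4,050 / 4) | 0.0003723 | 0.0003888 | 1.044 |

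The variance rises by about 4%. That is far less than 13%, because in December 2027 all four clusters are exposed and the month offers no concurrent control comparison.

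**Step 5: the 6-month use measure.** For the last cluster, transition starts on 1 July 2027 and exposure on 1 October 2027.

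- Counted from the end of transition, 6 months is reached about 1 April 2028, three months after the stated end.
- Counted from the start of transition, it is reached about 1 January 2028, just as the trial closes.

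With even steps, the third cluster completes 6 months after transition only at the close of 31 December 2027. Moving the record window from 1 to 31 December changes none of the last cluster's dates.

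**The case against.** The strongest reply is that this is a one-character slip: 1 December for 31 December. Nothing else in the article plans a 17-month extraction. Trial status also concerns recruitment and says its date is approximate, so it is not an exact end of extraction. Both points are fair. The conflict nevertheless stands on the sequence lengths alone, since 12 + 3 + 3 months does not fit into 17.

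A reader might infer from the 13% drop, or from the last cluster losing a third of its exposed time, that power is materially damaged. The documents do not support that: the time-adjusted variance rises only about 4%. A reader might also infer that Table 4 was built on 17 months and must be redone. Table 4 is not shown, so this is unknown.

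On sustainability, three stronger readings are tempting and none holds.

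- **That the December date causes the gap.** It does not. The measure is nurse-reported, lies outside the record window, and has the same problem with a 31 December end.
- **That the last cluster can never supply a 6-month figure.** The discussion of methodological risks applies the 3 to 12 month range to most outcomes, not all, so a later survey is not excluded. It is simply not stated, and the full protocol may give survey timing.
- **That sustainability as a whole would rest on the early clusters without saying so.** The article does not describe how the measure is pooled, and continued use of the training programme can be measured in every cluster.

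**Conclusion.** The point holds as two separate items of modest size.

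1. **Date conflict (firm).** The window in Sample size is 17 months, against 18 from the sequence lengths and an approximate end of 31 December 2027 in Trial status. Followed literally, it costs every cluster one exposed month and leaves the last cluster 2 months against a minimum of 3. This is a matter of consistency in a window that four hypotheses rely on. The cost in precision is about 4% in variance under the model in Step 4, and the likely cause is a misprint.

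2. **Six-month use measure (less certain).** Within the stated schedule, the last cluster has 3 months after transition, so nurse-reported use at 6 months or more does not fit and no later survey is stated. How far it misses depends on the undefined starting point. The training-programme component is unaffected.

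The 30 and 26 cluster-months, the third cluster's dates and the 4% rest on even 3-month steps. The 17 against 18 months and the last cluster's position need only the text and a common calendar.

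**What to change.** - **Sample size:** change the window for H1, H2, H3 and H6 to 1 July 2026 to 31 December 2027, so that it agrees with the Phase 3 design and Trial status. Confirm which duration Table 4 used, and revise it only if it used 17 months.
- **Implementation fidelity (H7):** state the date from which the 6 months are counted. Restrict the nurse-reported use component to clusters with at least 6 months of exposure on that definition, and report the last cluster's 3-month figure separately. Leave the training-programme component as it is.

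The cost is one date, one or two sentences and a check of Table 4. The extra month of routine extraction already lies inside the trial period, and recruitment is not due to start until July 2026.

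### The 80% power comes from a complete stepped-wedge formula with no term for the unobserved 3-month transition; if no allowance was made, the same sample gives about 55–56%

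*Protocol article*

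**What the plan says.** The Sample size section reads: "Sample sizes were calculated with an assumed intra-class correlation of 3%, 5% significance (two-tailed) and 80% power", "applying Woertman’s SW design estimate approach". The abstract repeats the same ICC, significance level, power and method. H1, H2, H3 and H6 are sized together, with the largest of their sample sizes used, on record and cost data "for the period of 1 st July 2026 to 1 st December 2027".

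The design is fixed elsewhere in the article:

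- Randomisation: "Each cluster will be randomly allocated to one of four starting dates for implementation". There are four clusters, so one per sequence.
- Fig. 3 caption: "Each sequence comprises a 3- to 12-month baseline control condition, a 3-month intervention transition period, and a 3- to 12-month intervention exposure condition".
- Phase 3, Study design: "Data gathered during the pre-intervention phase will be directly compared with data collected post-implementation".
- Table 3: the Implementation column carries a dash for outcomes 1–12. Only outcome 13 (fidelity) is collected then.

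The sample sizes themselves are in Table 4, which is not visible in the text at hand. Nothing in the visible text mentions an allowance for the transition.

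**The concern.** Woertman's design effect takes the number of steps, the baseline measurements, the measurements per step, the number of patients per cluster-period and the ICC. It assumes that each cluster moves from control to intervention between two adjacent observed periods. A period in which a cluster is in neither condition and contributes no data cannot be entered.

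In a stepped wedge the intervention is separated from calendar time by periods in which some clusters are in control while others are in intervention. A transition gap removes cells next to the switch, which carry much of that information. A sample size from the complete-design formula is then too small for the power attached to it.

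At stake is the reading of the main results. A trial described as having 80% power for its target effects may have appreciably less, and readers will use the stated figure when they interpret an inconclusive result.

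**Working it through.** **Inputs from the article.** ICC 0.03; two-sided 5%; power 80%; four clusters on four start dates; control 3–12 months, transition 3 months, exposure 3–12 months; no transition data for outcomes 1–12.

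**Inputs assumed.** Equal 3-month steps, with k = 4 steps, b = 1 baseline period and t = 1 measurement per step. Cell size n is not visible and is varied.

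**Layout.** Equal steps give 18 months, or six quarters (C control, T transition and unobserved, I intervention):

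| Sequence | 1 | 2 | 3 | 4 | 5 | 6 |
|---|---|---|---|---|---|---|
| First | C | T | I | I | I | I |
| Second | C | C | T | I | I | I |
| Third | C | C | C | T | I | I |
| Fourth | C | C | C | C | T | I |

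Only the third quarter (one intervention, two control clusters) and the fourth (two intervention, one control) contain both conditions. In the complete 4 × 5 layout, three of five periods do.

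**Step 1: the stated method.** The absolute sample size cannot be reproduced without Table 4, but the formula can be evaluated:

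DE = [1 + ρ(ktn + bn − 1)] / [1 + ρ(ktn/2 + bn − 1)] × 3(1 − ρ) / [2t(k − 1/k)]

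At n = 100: (1 + 0.03 × 499) / (1 + 0.03 × 299) × 2.91 / 7.5 = (15.97 / 9.97) × 0.388 = 0.6215. Multiplied by the five periods this is 3.11 (3.22 at n = 1000). It equals the generalised-least-squares variance of a complete 4-cluster by 5-period design with period effects and a random cluster effect; the ratio is 1.000 for every n tried from 5 to 3037. The formula is therefore the complete design.

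**Step 2: the same sample on the actual layout.** Keep 20 observed cells, the same n, period effects and ICC, and leave the T cells empty. The quantity that was 3.11 becomes 5.46 at n = 100, and 3.22 becomes 5.64 at n = 1000. The effect size is the one that gives exactly 80% power on the complete layout, so

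power = Φ[(1.96 + 0.8416) / √ratio − 1.96]

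| n per cell | Variance ratio | Power |
|---|---|---|
| 5 | 1.82 | 54.6% |
| 20 | 1.78 | 55.6% |
| 100 | 1.76 | 56.1% |
| 3037 | 1.75 | 56.3% |

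At n = 100: 2.8016 / √1.758 = 2.113, and Φ(0.153) = 0.561. The result hardly depends on n, so the unseen sample size is not needed for it.

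**Step 3: sensitivity of this figure.**

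- ICC 0.001 to 0.10: 54–56%.
- Monthly rather than quarterly periods: 56%.
- A window ending 1 December 2027 (17 months; Trial status gives about 31 December): about 55%.
- Unequal annual admissions from Table 2, over all orders of clusters: 54–58%.
- Wards as the clusters, using Table 2's ward counts: 52–59%.

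**Step 4: separate sensitivities, not part of the 55–56%.**

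- Degrees of freedom. A t-test on the transition layout gives about 24% at 2 df, 31% at 3 df, 37% at 4 df and 48% at 10 df (20 cells − 6 periods − 3 cluster contrasts − 1 treatment). The complete layout at 11 df already falls to 72%.
- Decay of correlation between periods. With an assumed cluster autocorrelation of 0.9 or 0.8, and the effect still set at 80% under no decay, power is as follows:

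| n per cell | Complete layout | Transition layout |
|---|---|---|
| 100 | 69% / 61% | 46% / 39% |
| 1000 | 29% / 18% | 18% / 12% |

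If the complete layout is instead set to 80% with the decay included, the gap alone again gives 55–56%.

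**The case against.** **Table 4 and Fig. 3 are not visible.** The inputs used, and any inflation for the transition, cannot be seen. This stands, and the figure is conditional for that reason. At 100 per cell, an inflation of 1.5 times would give 73% and 1.8 times would give 80%. However, the visible text names the method without qualification.

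**A reader might infer a still lower figure, such as 48%, as the correct one.** The documents do not support that. The Statistical methods section names no degrees-of-freedom method, 48% follows only from 10 df, and part of the loss occurs in a complete design too.

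**A reader might also attribute the very low values under correlation decay to the transition.** At 1000 per cell most of that fall occurs without any transition, and the autocorrelation is an assumption that appears nowhere in the article.

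**The shortfall need not apply to every hypothesis.** The largest sample size among H1, H2, H3 and H6 is used, so those that needed fewer start above 80%. H4 and H5 rest on surveys and a record sub-sample, and the text does not show that they fill every cluster-quarter equally. This stands.

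**The Statistical methods section names no period effect.** This is true. Without one, nominal power on the transition layout would be about 99%, but the intervention would be confounded with calendar time. Woertman's formula itself assumes period effects, so they are the right basis for checking a figure derived from it.

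**Conclusion.** The concern holds in conditional form. The stated method describes a complete stepped wedge, and the stated design is not one. If the formula was applied with k = 4, b = 1, t = 1 and no allowance for the transition, the same sample has 1.75–1.82 times the variance and about 55–56% power instead of 80%, under period effects, an exchangeable ICC of 0.03 and a normal test.

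The shortfall binds for whichever of H1, H2, H3 and H6 set the shared sample size, and for any other hypothesis sized to exactly 80% and collected on this layout. It would be too strong to say that the trial as a whole has 56% power: that would need the contents of Table 4.

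**What to change.** Recompute power, or the detectable effect at the planned sample size, on the actual layout of four clusters by six quarters with empty transition cells and period effects. State the steps, baseline periods, measurements per step and cell sizes used, and whether the sample size already allows for the transition. Show sensitivity to a named degrees-of-freedom method and to cluster autocorrelation, as separate lines. For H4 and H5, use the layout on which they will actually be collected. Then restate the figure in the abstract, the Sample size section and Table 4.

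This takes a few hours of calculation and needs no additional enrolment. Recruitment is scheduled to begin in July 2026, so it can be settled before any outcome data exist. The downside is a less favourable stated power.

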**Table 4 Tab4:**
[figure not shown]
Sample size calculations for seven hypotheses showing the target total and per arm (per data collection period) sample sizes

α =0.05, *β* = 0.20; *ICC* intra-class correlation

#### Data collection

Several outcome measures will be collected from a variety of data sources during the control and intervention periods to evaluate the effectiveness of HIRAID® Inpatient and address the study hypotheses. Data will be collected from the patient health records made available by each ward, from patients, carers of patients, nurses, medical staff and the nurse facilitators who are employed to deliver the HIRAID® Inpatient training. Data collected on patient experience, record reviews, and staff surveys will be collected and directly entered into REDcap™ (Research Electronic Data Capture) (https://catalyst.harvard.edu/services/redcap/), a secure web-based application for data management and survey tool, managed by the University of Sydney. The type of data that will be collected from each of these sources, and when they will be collected, are summarised below and in Table 5.

**Table 5 Tab5:** Summary of the data to be collected from each population at pre- and post-intervention, and the instrument that will be used

Population	Pre-intervention (baseline)	Post-intervention (outcomes)	Instrument
Nurses	Behavioural diagnostics		Theoretical domain framework, focus groups
		HIRAID® Inpatient evaluation and feedback	Feedback survey
	Satisfaction with communication and handover		Satisfaction with communication survey
	Perception of factors that influence nursing care		Practice Environment Scale of the Nursing Work Index
	Quality and quantity of nursing documentation		Modified D-Catch Tool
	Confidence in communication		Confidence with communication survey
Patients/Carers	Satisfaction with nursing care		Schmidt's Perceptions of Nursing Care Survey
	Experience		Australian Hospital Patient Experience Question Set
Medical and Allied Health staff	Satisfaction with communication and handover		Satisfaction with communication survey
Patients	Health data		Patient health records
	Satisfaction with nursing care		Schmidt's Perceptions of Nursing Care Survey
	Experience		Australian Hospital Patient Experience Question Set
Nurse facilitators	Implementation fidelity		Implementation fidelity survey

